## Abstract

**Background:**

Hamstring injuries are the most common muscle injury in amateur and professional soccer. Most hamstring injuries occur in the late swing phase, when the hamstring undergoes a stretch-shortening cycle and the hamstring does a significant amount of eccentric work. The incidence of these injuries has not decreased despite there being effective injury prevention programmes focusing on improving eccentric hamstring strength. As this might be because of poor compliance, a more functional injury prevention exercise programme that focuses on the stretch-shortening cycle might facilitate compliance. In this study, a bounding exercise programme consisting of functional plyometric exercises is being evaluated.

**Methods:**

A cluster-randomized controlled trial (RCT). Male amateur soccer teams (players aged 18–45 years) have been randomly allocated to intervention and control groups. Both groups are continuing regular soccer training and the intervention group is additionally performing a 12-week bounding exercise programme (BEP), consisting of a gradual build up and maintenance programme for the entire soccer season. The primary outcome is hamstring injury incidence. Secondary outcome is compliance with the BEP during the soccer season and 3 months thereafter.

**Discussion:**

Despite effective hamstring injury prevention programmes, the incidence of these injuries remains high in soccer. As poor compliance with these programmes may be an issue, a new plyometric exercise programme may encourage long-term compliance and is expected to enhance sprinting and jumping performance besides preventing hamstring injuries.

**Trial registration:**

NTR6129. Retrospectively registered on 1 November 2016.

## Background

Thirty-one percent of all injuries in male soccer players are muscle injuries, which account for 27% of injury-related time off soccer [1, 2], and 37% of all soccer-related muscle injuries are hamstring injuries. These injuries can be classified as high-speed running injuries and stretching injuries [1, 3, 4], with the sprint-type injury being the most common type of hamstring injury in soccer [2–5]. Hamstring injuries also have the highest re-injury rate and are associated with the longest time off play and training (>28 days) [1, 2, 6]. Although several intrinsic and extrinsic risk factors have been identified, to date the incidence of hamstring injuries has not diminished [6–11].

Sprint-type hamstring injuries mostly occur in the late swing phase [4, 5, 12, 13], when the hamstring muscles are maximally stretched during limb deceleration [4, 5, 13–16]. In the second half of the swing, the bi-articular hamstring muscles undergo a stretch-shortening cycle [14]. The greatest stretch is seen in the femoral biceps, which is the hamstring muscle most often injured [3, 5, 13, 14]. The stretched hamstring muscle actively contracts in the swing phase, which could indicate that the hamstrings contract eccentrically in the late swing phase [13]. In addition, it has been found that as the sprint speed increases, so too does the amount of stretch and negative work of the hamstring muscles [13]. Thus it has been suggested that increasing eccentric strength might reduce the risk of sprint-type hamstring injury.

Recent studies have shown that improving eccentric hamstring strength by means of the Nordic Hamstring Exercise (NHE) can reduce the incidence of hamstring injuries by 66–70% [16, 17]. Yet the incidence of hamstring injuries has not only not decreased in the past 10 years, but has actually increased by 4% [18]. This might be because these exercises are not performed correctly or because compliance is poor. A recent study among Champions league and Norwegian premier league teams confirmed this hypothesis: only 6% of the participating teams performed the NHE according the prescribed programme [19]. The same trend has been seen in Dutch soccer players [20], with most teams no longer performing the prevention programme 3 years after its introduction [20]. Arguments for non-compliance mentioned in the Netherlands are lack of time, delayed onset muscle soreness, the need to sit on the ground or a mat, and not sport- specific enough to incorporate into the warming-up [20].

The bounding exercise programme (BEP) is another potentially effective training programme that can be done after warming-up. It consists of single leg jump exercises characterized by a stretch-shortening cycle: eccentric pre-stretch phase, amortization phase, and concentric shortening phase [21]. This stretch-shortening cycle strengthens the elastic properties of connective tissue, thereby improving (eccentric and concentric) strength and power by allowing the muscle to accumulate (pre-stretch / eccentric phase) and release (concentric phase) energy [22, 23]. Specific physiological adaptations induced by plyometric training are increased motor unit activation, increased passive tension of the muscle- tendon complex, and improvement of cross-bridge mechanics [24, 25]. These adaptations are associated with improved strength, increased joint stiffness, and improved neuromuscular control and functional performance [26–28]. Plyometric training is already used widely in intermittent team sports in order to enhance sprinting and jumping performance [22, 29–35] and might reduce sprint-type hamstring injuries.

In summary, hamstring injuries are a major health problem in soccer and their incidence has increased over recent years, despite there being effective prevention programmes. This is possibly because of poor compliance. There is an urgent need for a functional, short, easy-to-implement, sport-specific hamstring injury prevention programme that includes eccentric and plyometric exercises, so as to improve the performance of sport-specific tasks, such as sprinting and jumping, and which is likely to be adopted. The BEP could fulfil this need. The aim of this hamstring injury prevention study-3 (HIPS-3) is to investigate the preventive effect of a BEP on hamstring injuries in male amateur soccer players. The secondary aim is to investigate compliance with this programme during the soccer season 2016–2017 and at the start of the soccer season 2017–2018.

## Methods/design

### Design and study setting

This prospective, cluster-randomized trial was designed in accordance with the guidelines of the Standard Protocol Items: Recommendations For Interventional Trials (SPIRIT) [36]. The study is being carried out in cooperation with the University Medical Centre of Utrecht and the Royal Netherlands Football Association (KNVB) in Zeist (the Netherlands). As the BEP is being investigated in a real-life setting, soccer teams from four different districts, playing in Dutch first-class amateur field soccer competition, were invited to participate in this study. These teams usually play one (or two) matches a week, with 2–3 training sessions per week. Each district has two competitions at first-class level.

### Recruitment of participants and randomization

Dutch male soccer players (age 18–40 years) playing in the Dutch first-class amateur competition were eligible for participation. All players were asked to give their written informed consent before the start of the study. Players who did not give their informed consent, who joined a team after the start of the study, or who had a lower than average understanding of Dutch were excluded.

After selection of the four districts, a top-down strategy was carried out to recruit the soccer teams. First, the boards of the clubs were informed about the study by means of an email from the director of amateur soccer of the KNVB and the research team. Then the members of the medical staff and the coaches were invited, by telephone, to attend a meeting to tell them about the purpose and methods of this study. If the clubs decided to participate in this study, all players of the participating teams received an information letter including an informed consent form. To avoid a risk of contamination, the teams were randomized as clusters instead of individual players [37]. Randomization was done independently by an online randomizer (https://www.randomizer.org/) and an equal number of teams were assigned to the intervention and control groups. After randomization, meetings were organized in each district to inform staff and players in the intervention group about the BEP.

### Intervention

The intervention group is performing the BEP during the entire 2016–2017 outdoor soccer season. In the first 12 weeks, there is a gradual build up of walking lunges, triplings and drop lunges, and bounding (alternating leg jumps) (Table 1).

**Table 1 Tab1:** BEP Program

Week	Programme
1	2x30m walking lunges (2 × 10)
2	3x30m walking lunges (3 × 10)
3	3x30m walking lunges +1x30m triplings + droplunges)
4	2x30m triplings + droplunges (2 × 10)
5	3x30m triplings + droplunges (3 × 10)
6	3x30m triplings + droplunges +1 × 30 m bounding
7	2x20m bounding (+/− 7 jumps)
8	3x20m bounding (+/− 7 jumps)
9	4x20m bounding (+/− 7 jumps)
10	3x30m bounding (+/−10 jumps)
11	4x30m bounding (+/− 10 jumps)
12	4x30m bounding (in the least possible jumps)
13 untill end of competition	3x30m bounding (in the least possible jumps)

This gradual build-up from basic concentric strength exercise to eccentric strength exercise followed by plyometric exercise should improve functional movement patterns and increase strength [38]. All exercises are performed over a distance of 30 m in accordance with the SCORE project, which uses another form of bounding, focusing on vertical stability [39]. After the build-up phase, participants continue with the BEP during warming up in two training sessions and follow a prescribed intensity training programme. After the winter break, when there is no structural training, teams will restart the BEP. In order to compensate for potential de-training effects [40–42], starting with the same programme as performed in week 6. If a player is injured at the start of the programme and recovers from this injury, he re-starts the BEP programme. If a player is injured in weeks 1–6 and achieves full recovery within 4 weeks, he re-starts the BEP at −1 week (i.e. a player injured in week 4 and who achieves full recovery within 4 weeks re-starts the BEP in week 3). If a player is injured in weeks 7–13 and achieves full recovery within 4 weeks, he re-starts the BEP in week 6. If an injury last longer than 4 weeks, the player is asked to contact the research team before resuming the BEP (Table 2).

**Table 2 Tab2:** Restarting BEP after injury

Week nr. BEP of Injury occurrence	Period of injury (weeks)	Restarting BEP
1–6	<4	Week injury occurrence −1
1–6	>4	Contact with research team
7–13	<4	Week 6
7–13	>4	Contact with research team

#### Walking lunges (Fig. 1)

The player starts in a standing upright position and steps forward with the right leg. From this position, the left knee moves downwards to the ground while the upper body remains upright. This movement is followed by a step forward passing the right foot. From this second position, the right knee moves downwards to the ground, followed by a step forward passing the left foot, etc. It is important that the flexion of the leading knee does not exceed 90 degrees, and that the shoulder, hip, and knee of the back leg are in a vertical line [43].

**Fig. 1 Fig1:**
[figure not shown]
Walking lunges

#### Triplings followed by drop lunges (Fig. 2)

Triplings are a classic running exercise. The player starts in a standing position and initiates a fast small step forward and lands on his forefoot, followed by the other leg. This sequence is repeated 4 times. At the same time, the player performs a fast arm swing, After 4 repetitions, the player jumps vertically jump and lands in the end-position of the lunge [43].

**Fig. 2 Fig2:**
[figure not shown]
Triplings followed by drop lunges

#### Bounding (Fig. 3)

The bounding exercise, in the literature referred to as ‘a running bound’ or ‘alternate leg bounding’, is a popular running-specific exercise that can be categorized as plyometric exercise. These plyometric exercises contain three phases: the eccentric pre-stretch, the amortization phase (time between eccentric and concentric contraction), and the concentric shortening phase [21]. The player starts running and after 3 m he performs horizontal jumps (bounding). The focus of this exercise is to achieve horizontal position of the femur in swing-phase, a full foot landing, and as fast as possible horizontal speed. The running start is chosen to reach a maximum speed in bounding by getting a maximum hamstring musculo-tendon stretch and force [13]. All players have to cover 30 m excluding the 3 m running start.

**Fig. 3 Fig3:**
[figure not shown]
Bounding

### Implementation procedures

The medical staff and/or coaches of the intervention teams were instructed how to implement the BEP during the above-mentioned instruction meetings. During these meetings, there was a video presentation of the BEP programme, followed by a live demonstration on the soccer field. Emphasis was on key aspects of the intervention and the performance of the exercises. All coaches and medical staff received the instruction-video and instructions by email and in writing.

The research team is always accessible to answer questions by telephone or email. All participating teams are visited, and the medical staff has been asked to record the intervention on camera (cell phone) and to send the recording to the research team for analysis and feedback, at least every 3 weeks in the build-up phase. The BEP is performed at the end of the warming-up. Coaches and medical staff were advised to allow a short active recovery period before the rest of the training session if players complain of tired legs.

### Data collection

#### Baseline characteristics

All participants were asked to complete a questionnaire on baseline characteristics, namely, date of birth, nationality, height, weight, years of experience as a soccer player, field position, leg dominance, preventive measures for hamstring injuries, preventive measures for other injuries, study load/ workload and capacity, hours of sleep, hours of travel, current state of the hamstring muscles in relation to activities, and injury history.

#### Exposure, injuries, and compliance

Exposure, injuries, and compliance are self-reported weekly throughout the entire soccer season (39 weeks), with players being allowed to choose whether they prefer to register by SMS or by e-mail (NetQ). Each Monday, all players receive four short questions regarding how long they have trained (minutes), how long they have played in a match (minutes), and whether they have had a hamstring injury or another’ injury. The players in the intervention group receive a fifth question regarding the amount of BEP they have performed in the past week.

Injuries are divided into hamstring injuries, other injuries, and recurrent (hamstring) injuries. A hamstring injury is defined as any physical complaint affecting the posterior side of the upper leg resulting in an inability to play or train regardless of the need for medical attention or time off soccer-associated activities [44]. In the case of a hamstring injury, both the player and the medical staff separately fill in a hamstring injury questionnaire to record epidemiology, severity, and aetiology of the injury. Other injuries are defined as any physical complaint, other than affecting the posterior side of the upper leg, that results in an ability to play or train regardless of the need for medical attention or time off soccer-associated activities [44]. Other injuries are recorded for measuring exposure and are not further specified by an injury follow-up questionnaire. Recurrent injuries are defined as an injury of the same type and at the same site as an index injury occurring after a player has returned to full play/training. In the case of a recurrent hamstring injury, the player and medical staff will receive the same hamstring injury questionnaire as for the primary hamstring injury.

Exposure (in minutes) is divided into match play and training sessions. Training exposure is defined as team-based and individual physical activities under the guidance of the team’s coaching or fitness staff that are intended to maintain or improve players’ soccer skills or physical condition [44]. Match play is defined as a play between two different teams [44].

Intervention compliance is measured weekly by SMS or email (NetQ). The number of metres of the BEP performed is registered as metres/week. Compliance is expressed as a percentage by dividing the meters BEP performed by the metres mentioned in the programme. At the end of the study period, overall compliance will be investigated by means of a self-administered questionnaire.

Long-term compliance with the BEP will be measured once, at the start of the new soccer season 2017–2018. All players in the intervention group will be asked how many metres BEP they performed in that week and how many days ago their last bounding session was (Figs. 4 and 5).

**Fig. 4 Fig4:**
[figure not shown]
Study procedure

**Fig. 5 Fig5:**
[figure not shown]
SPIRIT figure

### Outcomes

The primary outcomes are the incidence and severity of hamstring injuries. The secondary outcome is compliance with the BEP. The hamstring injury incidence is recorded per 1000 h of exposure, and severity is operationalized as the number of days since the day of injury and the day of full return to play [17]. Compliance is expressed as a percentage of BEP completion.

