### Sample size

The sample size was calculated based on previous studies. Earlier findings showed a reduction in hamstring injury incidence of up to 70% with eccentric training of the hamstring muscle, an injury incidence of 1 in 11 players per soccer season, and recurrence rates of 12–30% [16, 17]. On the basis of these findings and two-sided testing, significance level of 0.05, power 0.8, an inflation correction for cluster randomization of 1.19, drop-out of 20%, and loss to follow-up of 20%, we calculated that 26 teams of approximately 16 players would have to be included. Taking into account that the follow-up period is in a new soccer competition, with a larger loss to follow-up, we included 10% extra players, so that in total the study includes 30 teams with about 16 players/team (*n* = 480).

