### Statistical methods

SPSS version 22 will be used to analyse the data. Descriptive statistics will be used to analyse the baseline characteristics. The incidence of hamstring injuries will be analysed on an intention-to-treat basis. The primary outcomes will be compared in the intervention and control groups using Chi square tests, Poisson general log-linear analysis, and Cox regression analysis with survival curves.

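### The primary outcome is incidence alone in the Abstract but incidence plus severity in Outcomes, and severity as defined has a value only for injured players

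*Protocol article*

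**What the plan says.** The article gives two answers on what decides the trial.

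- Abstract, Methods: "The primary outcome is hamstring injury incidence".
- Outcomes: "The primary outcomes are the incidence and severity of hamstring injuries". The same section defines the second of these: "severity is operationalized as the number of days since the day of injury and the day of full return to play".
- Statistical methods: "The primary outcomes will be compared in the intervention and control groups using Chi square tests, Poisson general log-linear analysis, and Cox regression analysis". The plural means that severity, if primary, is to be compared between groups and not only described.

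Two other statements refer to incidence only.

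- Sample size uses "a reduction in hamstring injury incidence of up to 70% with eccentric training of the hamstring muscle" and "an injury incidence of 1 in 11 players per soccer season", with "two-sided testing, significance level of 0.05, power 0.8, an inflation correction for cluster randomization of 1.19". It gives no expected difference or standard deviation for days to return.
- Statistical methods: "The incidence of hamstring injuries will be analysed on an intention-to-treat basis". It does not say which players enter a comparison of severity.

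**The concern.** These are current statements in the same article, so this is a contradiction and not a detail left to a fuller document. A reader cannot tell whether a neutral result on incidence with a favourable result on severity would count as success, or the reverse.

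Two separate problems follow if severity stays primary. The first is multiplicity: two primary outcomes share one stated alpha. The second is the comparison itself. Days to return exist only for a player who has been injured, and injury is what the programme aims to prevent. If the programme works, the injured players in the two groups were selected differently after randomization, and their days per injury may differ for that reason alone.

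**Working it through.** **1. What the stated size covers.** Inputs from Sample size: control risk 1/11 = 0.0909; risk after a 70% reduction 0.3/11 = 0.0273; two-sided alpha 0.05; power 0.80; design effect 1.19; drop-out 20%; loss to follow-up 20%. The pooled two-proportion formula is

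n per arm = [1.96·√(2p̄q̄) + 0.842·√(p₁q₁ + p₂q₂)]² / (p₁ − p₂)²

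With p̄ = 0.0591 this gives 215 per arm. Then 2 × 215 × 1.19 = 512, and 512/(0.8 × 0.8) = 800 players, or 50 teams of 16. The article states 26 × 16 = 416. The stated figure is therefore not reproduced as a total from all the stated inputs. That is a separate matter and nothing below depends on it. What counts here is that every input concerns incidence. The steps below use only the final size, 480 players in 30 teams with equal numbers of teams per group, so 240 players per group.

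**2. Error rate under each possible success rule.**

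- Either outcome suffices, each at 0.05, independent tests: 1 − 0.95² = 0.0975. The bound for any dependence is 0.05 + 0.05 = 0.10.
- Either suffices, correlated tests (simulated): 0.095 at correlation 0.3, 0.091 at 0.5, 0.078 at 0.8.
- Both must succeed: at most 0.05, so no inflation.
- Incidence alone with one lead test: 0.05.

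**3. How many players would have a severity value.** Control: 240/11 = 21.8. Intervention: 21.8 × 0.3 = 6.5. That is about 28 of 480 players, counting players with a first injury and before attrition. Two adjustments give a range:

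- Adding the stated 12–30% recurrence as further injuries: 21.8 × 1.12 to 21.8 × 1.30 = 24 to 28 against 6.5 × 1.12 to 6.5 × 1.30 = 7 to 8.5.
- Worst case, if every player lost contributes no injury: × 0.64 gives 14 against 4.

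**4. What such a comparison could detect.** The standardized difference detectable with 80% power is 2.80 × √(1/21.8 + 1/6.5) = 1.25 SD, and 1.56 SD in the worst case. Both are optimistic, because they ignore clustering and small-sample critical values. They show lack of power and say nothing about bias.

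**5. Can days per injury move with no effect on injury length?** The distributions here are assumed; the article gives none. In both examples 70% of injuries are prevented overall and each remaining injury lasts as long as it would have anyway.

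*Two-point example:* half of control injuries last 7 days and half 35, so the control mean is 21.

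- 80% of short and 60% of long injuries prevented: 0.1 short and 0.2 long remain per control injury. Mean = (0.1 × 7 + 0.2 × 35)/0.3 = 7.7/0.3 = 25.7 days, so it rises. Days lost per player fall to 7.7/21 = 0.37 of control.
- 60% of short and 80% of long prevented: mean = (0.2 × 7 + 0.1 × 35)/0.3 = 4.9/0.3 = 16.3 days, so it falls. Days lost per player fall to 4.9/21 = 0.23 of control.

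*Lognormal example:* median 21 days, SD of log-days 0.8.

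- 80% of injuries below the median and 60% above it prevented: the new median is the 62.5th percentile of the control distribution, 21 × exp(0.8 × 0.319) = 27 days.
- Reversed: the 37.5th percentile, 21 × exp(−0.8 × 0.319) = 16 days.
- 70% prevented in both halves: the median stays at 21.

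The contrast moves only when the programme changes which injuries occur, and it can move in either direction.

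**The case against.** The strongest reply is that the article already leans towards incidence. Its aim is prevention, its size rests on incidence, and its intention-to-treat sentence names incidence. On that view the Outcomes sentence is a loose phrase, and an analysis plan not shown here may fix the rest. The lean is real, and it supports the remedy. It does not remove the contradiction, because Statistical methods repeats the plural.

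Three stronger readings are tempting, and the article does not support them.

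- *That the plan doubles the false-positive rate.* This needs an either-outcome rule and nearly independent tests. The article states no success rule, and a both-must-succeed rule would not inflate alpha. The 9.75% is conditional.
- *That severity cannot be analysed by intention to treat.* This is true only of days per injury. Days lost can be defined for every randomized player, with zero for the uninjured. Nor does the intention-to-treat sentence show that severity was deliberately left out; that would be inference from silence.
- *That the severity comparison is invalid in any event.* If the programme has no effect on who is injured, the injured groups are comparable. The selection problem arises when the programme works, and it is distinct from the multiplicity problem.

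The count of 14 against 4 is also a worst case, since weekly reporting lets players who leave early contribute injuries. No passage says whether milder or severer injuries would be prevented more often, so the examples show what is possible and do not forecast it.

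**Conclusion.** The concern stands in this form. The Abstract and the Outcomes section disagree on the primary outcome, and the sample size and the intention-to-treat statement match only the Abstract. If severity remained co-primary, one of two consequences would follow. Under an either-outcome rule the familywise error would reach 9.75% for independent tests, less when they are correlated. Under a both-outcomes rule the error rate would hold, but success would depend on about 28 first-injured players (22 against 6 to 7) in a comparison for which the trial was not sized. Under either rule, days per injury is open to selection bias to the extent that the programme changes who is injured. The counts assume 480 players, 1 in 11 injured in control, a 70% reduction and no attrition.

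**What to change.** State hamstring injury incidence as the single primary outcome in both the Abstract and Outcomes, and use the singular in Statistical methods. Make severity secondary and define it for all randomized players as hamstring days lost per player over the season, zero if uninjured, analysed with allowance for team clustering and for skewed counts. A rate per exposure hour is less suitable for this outcome, because exposure falls while a player is injured and the denominator then depends on severity. Say how injuries unresolved at season's end and players followed for only part of the season are counted. Report days per injury by group descriptively.

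The cost is a few sentences of rewording, using injury and return dates that the stated definition of severity already requires. The downside is that no primary claim on severity is possible. The alternative of keeping both as primary with alpha split to 0.025 each costs more: incidence alone would then need 260 rather than 215 players per arm before inflation (260/215 = 1.21, so 21% more), and the selection problem in days per injury would remain.

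### The article does not say whether recurrent injuries count in the primary incidence, or which of chi-square, Poisson and Cox decides it

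*Protocol article*

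**What the plan says.** The Abstract of the protocol article names one primary outcome: "The primary outcome is hamstring injury incidence". The Outcomes section names two: "The primary outcomes are the incidence and severity of hamstring injuries". For the first it adds: "The hamstring injury incidence is recorded per 1000 h of exposure". That gives the scale of measurement but not the events in the numerator.

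The section on exposure, injuries and compliance makes recurrences a class of their own: "Injuries are divided into hamstring injuries, other injuries, and recurrent (hamstring) injuries". The definition reads "Recurrent injuries are defined as an injury of the same type and at the same site as an index injury", and applies once the player is back in full play or training. For a recurrent hamstring injury, "the player and medical staff will receive the same hamstring injury questionnaire as for the primary hamstring injury". A first-injury count and an all-injury count can therefore both be built from the same data.

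The Sample size section plans on "an injury incidence of 1 in 11 players per soccer season, and recurrence rates of 12–30" per cent, with a single two-sided significance level of 0.05. The Statistical methods section says: "The primary outcomes will be compared in the intervention and control groups using Chi square tests, Poisson general log-linear analysis, and Cox regression analysis". Survival curves are to accompany the last of these. The section does not say which method serves incidence and which serves severity, and it ranks none of them.

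**The concern.** In their usual form the three methods answer different questions. Chi-square compares the proportion of players injured and ignores exposure. Poisson compares a rate per unit of exposure and can take every injury. Cox compares the time to a first injury. With none named as deciding and the counted event left open, a claim of success could rest on whichever result is favourable.

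A second problem lies inside the Poisson option. If it counts recurrences, two injuries in one player are treated as independent. The default variance is then too small and the test rejects too often by itself.

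The article says that teams had already been allocated and that registration was retrospective, so a clear public statement of the deciding analysis carries more weight than usual.

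**Working it through.** **Inputs from the article.** 30 teams × 16 players = 480, so 240 per arm with equal allocation of teams. Control risk p = 1/11 = 0.0909 per player-season. Recurrence proportion q = 0.12 to 0.30. Two-sided level 0.05.

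**Assumptions not in the article.** At most one recurrence per injured player; exposure varying between players by about 30% of its mean; no team effect.

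**1. How much the counted event matters.** Expected control-arm events:
- injured players: 240/11 = 21.8
- all injuries: 21.8 × 1.12 = 24.4 to 21.8 × 1.30 = 28.4

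Counting recurrences adds 12% to 30% to the first injuries. Leaving them out removes 0.12/1.12 = 11% to 0.30/1.30 = 23% of all injuries.

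**2. Whether the sample size reveals the unit.** For two proportions, per arm, n = [1.96·√(2·p̄(1−p̄)) + 0.842·√(p₁(1−p₁)+p₂(1−p₂))]² / (p₁−p₂)². With p₁ = 1/11 and p₂ = 0.3/11 this gives 215. In total, 2 × 215 × 1.19 = 512 players, or 32 teams before attrition, and 512/0.64 = 800, or 50 teams after it. Raising p₁ by 12% or 30% as a rough way to count every injury gives 44.2 or 37.7 teams after attrition. Neither unit yields the stated 26 teams, so that figure cannot be used to infer which unit was meant. Why it does not reproduce is a separate question.

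**3. False positives of a default-variance Poisson test on all injuries.** A player contributes 0, 1 or 2 injuries, with mean p(1+q) and mean square p(1+3q). The ratio of true variance to Poisson variance is therefore roughly (1+3q)/(1+q) − p(1+q):
- q = 0: 1 − 0.091 = 0.909. The critical value 1.96 acts as 1.96/√0.909 = 2.06, a level of 4.0%.
- q = 0.12: 1.214 − 0.102 = 1.113. It acts as 1.86, a level of 6.3%.
- q = 0.30: 1.462 − 0.118 = 1.343. It acts as 1.69, a level of 9.1%.

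**4. The three tests together, by simulation under no effect** (20,000 trials per setting):

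| Recurrence | Chi-square | Poisson, all injuries, default variance | Cox, first injury | At least one significant |
|---|---|---|---|---|
| none (all three on first injuries) | 5.1% | 3.8% | 5.1% | 5.6% |
| 12% | 5.1% | 6.0% | 5.2% | 7.5% |
| 30% | 4.9% | 8.6% | 4.8% | 9.5% |

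The Poisson column agrees with step 3. When 20% of players also have only partial follow-up, the last column becomes 7.6% to 10.3% with the default variance. With a robust variance for the Poisson rate it becomes 6.6% to 7.2%. Further runs with all three tests on first injuries gave 5.3% to 5.8%.

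**5. Disagreement when there is an effect.** At a rate ratio of 0.5, with Poisson counting recurrences at 12% to 30%, the three tests do not all reach the same side of 5% in about 10% to 14% of simulated trials.

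**The case against.** The strongest reply is that an article condenses its protocol, and that first versus all injuries and the choice of model are commonly left to an analysis plan. For detail that is merely absent, that is right. Here, however, the article itself commits the primary outcomes to three comparisons under one 0.05 level and makes recurrences a separate class. A later plan would have to narrow what is published.

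Four other points limit the concern:
- The scale is fixed as a rate per 1000 h, and of the three methods Poisson is the natural one for it. That favours Poisson but does not name it.
- A reader might infer that all three tests are primary for incidence. The Statistical methods section speaks of primary outcomes in the plural, and severity is one of them. Cox, for instance, could be meant for days to return to play. The text supports only that methods are not mapped to outcomes.
- A reader might infer that a player's first injury of the season, at a site injured in an earlier season, must be classed as recurrent. The definition refers to an index injury without saying whether it must fall in the study season. The comparison with the primary hamstring injury in the questionnaire rule can be read as one recorded in the study. The point is unclear and is not quantified here.
- A reader might see a contradiction in planning on players injured per season while reporting a rate. That is ordinary practice and no error.

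**Conclusion.** The concern holds in a limited form. Neither the event counted in the primary incidence nor the deciding analysis is fixed, and this should be settled before the groups are compared.

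The inflation is modest. The tests are strongly correlated, so the 1 − 0.95³ = 14.3% that three independent tests would give does not apply. Choosing among three tests of first injury adds little, about half a percentage point. Most of the rise to 7.5% to 9.5% comes from letting one test count recurrences with a default variance, which the article neither states nor rules out. The larger practical consequence is that at a rate ratio of 0.5 the conclusion can depend on the test in roughly one trial in eight.

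These figures isolate the effect of the open choice. They leave out team clustering, so they are not the error rates of this trial. They also take all three methods as applied to incidence.

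**What to change.** In the Outcomes and Statistical methods sections:
- State that the deciding incidence analysis is the rate ratio of first study-season hamstring injuries per 1000 h of exposure up to that injury, whatever the player's earlier history, from a Poisson model that accounts for team clustering.
- Label as supportive the proportion injured, Cox time to first injury, and the all-injury count with repeat events handled per player.
- State which method serves severity, and bring the Abstract and the Outcomes section into line on whether severity is primary.
- State that the index injury in the definition of recurrence is one recorded in the study season.

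No new data are needed. The cost is that recurrences leave the primary count: 21.8 expected control events instead of 24.4 to 28.4, about 11% to 23% fewer. For a 70% reduction with 480 players, a design effect of 1.19 and no attrition, power on injured players is 77.5%. Treating every injury as a separate independent event would suggest 82% to 88%, but this is a rough proxy that overstates the gain, because repeat injuries in one player are not independent. Counting all injuries would also be defensible if stated in advance with repeat events handled per player. First injuries are preferred here because they match the players-injured unit in the Sample size section.
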